**Methods:**

A total of 1026 patients will be included into this study. Cardiovascular research PLHIV with (*n* = 114 in each of the three recruiting centers) - or without - ART (*n* = 114 in each of the three recruiting centers) with COVID-19 and HIV-negative with COVID-19 (*n* = 114 in each of the three recruiting centers) will be carried out via clinical and biochemical measurements for cardiovascular risk factors and biomarkers of cardiovascular disease (CVD). Vascular and endothelial function will be measured by brachial artery flow-mediated dilatation (FMD), carotid intima-media thickness (IMT) assessments, and retinal blood vessel analyses, along with vascular endothelial biomarkers and cogualation markers. The correlation between HIV-infection in COVID-19 PLHIV with or without ART and its role in enhancement of cardiovascular risk and endothelial dysfunction will be assessed at admission, weekly, at discharge and, 4 weeks post-discharge (if possible).

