## Methods/design

### Study design

In the prospective ENDOCOVID study, monitoring will be carried out at admission (baseline), weekly, at discharge and, a follow-up 4 weeks post-discharge (if possible) (Figs. 1 and 2). The four- week post-discharge collection may be hampered by unpredictable lockdowns; therefore, this measurement may not be carried out in all the participants (that is why it is indicated as “when possible”). Measurements will include health questionnaires, anthropometric measurements, a cardiovascular physical examination, blood collection, Ultrasound-based vascular and endothelial measurements, and fundus imaging for retinal blood vessel analysis (Fig. 2). Results obtained at admission (baseline), weekly, at discharge and, 4 weeks post-discharge (if possible) (Fig. 1) will be compared. ENDOCOVID (protocol version 1 from August 13, 2020) has received ethics approval from Walter Sisulu University, South Africa (EC_202011_006 and 053/2020), as well as University of Illorin Teaching Hospital, Nigeria (NHREC/02/05/2010) and Lagos State University Teaching Hospital, Nigeria (NHREC04/04/2008). Protocol modifiers will be submitted to the respective ethics committees as well as to the clinical trial registration. Verbal and written informed consent will be obtained by the study clinician from each participant prior to being included into the study.

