#### Data collection, management and statistical analysis

Data from the questionnaires, clinical evaluations, and biochemical analyses will be gathered and managed by Research Electronic Data Capture (REDCap) tools hosted at the Walter Sisulu University [64] (Fig. 1).

Statistical analyses will be performed in collaboration with the Biostatistics Unit in the Centre for Evidence-based Health Care, Walter Sisulu University. Descriptive statistical models (ANOVA, Chi Square) will be used for inter-group comparisons, and associations between independent and dependent variables will be tested by multivariate regression analysis models, taking into account confounding variables such as age, gender, ethnicity, smoking, alcohol consumption, medication, and BMI. For long term changes in the same individual, a repeated measures model approach will be engaged.

Strijdom et al., in their discussion of the *EndoAfrica* study design, suggested that sample sizes of up to 300 participants are sufficient to secure statistical power [39]. Fischer’s formula was also used for calculation of sample size: (n) = Z2P (1-P)D2. Since there are no data on the number of people with coinfection of HIV and SARS-CoV-2, the sample size was calculated using the prevalence rate of PLHIV of 4.9% in SSA (UNAIDS report, 2019) [65]. To achieve statistical significance, 94 HIV-infected persons are required. Since we have 3 groups, we will require a total of (94 × 3) = 282 participants. Due to 20–30% drop out rate, 20 more persons in each group will be added to this number, so that the final number of participants required in this project has similar participant numbers that were recruited in the *EndoAfrica* study (282 + 60 = 342 at each recruiting center). Demographic and background data (e.g., smoking and drinking status, BMI) will also be collected and included in the linear regression models as putative confounders [66].

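### Adding 20 per group covers at most 17.5% loss, so 114 per group per centre does not keep the required 94 at the plan's own 20–30% drop-out

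*Protocol article*

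**What the plan says.** All the figures are in the protocol article, under 'Data collection, management and statistical analysis'.

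- **Requirement.** "To achieve statistical significance, 94 HIV-infected persons are required", followed by "Since we have 3 groups, we will require a total of (94 × 3) = 282 participants". The 94 rests on a single-proportion formula: "the sample size was calculated using the prevalence rate of PLHIV of 4.9% in SSA".
- **Allowance for loss.** "Due to 20–30% drop out rate, 20 more persons in each group will be added to this number".
- **Result.** "282 + 60 = 342 at each recruiting center", that is 114 per group at each centre. The Abstract (Methods) and 'Aim and objectives' repeat 114 per group per centre, and the Abstract gives the overall size: "A total of 1026 patients will be included into this study".

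The same sentence says the final number is meant to be similar to recruitment in the EndoAfrica study. On the visit four weeks after discharge, 'Study design' warns that "this measurement may not be carried out in all the participants".

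**The concern.** The paragraph presents three figures as one chain: a required number, an expected drop-out rate, and an addition made because of that rate. A reader will take it that 114 per group leaves at least 94 after the expected loss. An allowance for loss has to be found by dividing the required number by the proportion expected to remain. Adding about a fifth of the required number falls short of that.

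What is at stake is whether the stated size delivers what the plan calls required. If every centre recruits in full and loses patients as expected, each group at each centre ends below the plan's own figure, and the text gives no sign of it.

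**Working it through.** **Inputs, all from the sample-size paragraph except where noted**

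- Required per group, before loss: 94
- Expected loss d: 20% to 30%
- Added per group: 20
- Groups: 3; recruiting centres: 3 (Abstract)

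**Step 1. The plan's own figures.** 94 + 20 = 114 per group. 114 × 3 = 342 per centre. 342 × 3 = 1026 overall. All three reproduce exactly.

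**Step 2. Loss that the allowance covers.** 114 × (1 − d) = 94 gives d = 20/114 = 17.5%. This is below 20%, the lower end of the plan's range.

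**Step 3. Numbers remaining, and numbers needed to keep 94.** Remaining = 114 × (1 − d). Needed = 94/(1 − d), rounded up.

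| Loss d | Remaining per group per centre | Short of 94 by | Needed per group per centre | Per centre (× 3) | Overall (× 9) |
|---|---|---|---|---|---|
| 20% | 91.2 | 2.8 | 117.5 → 118 | 354 | 1062 |
| 25% | 85.5 | 8.5 | 125.3 → 126 | 378 | 1134 |
| 30% | 79.8 | 14.2 | 134.3 → 135 | 405 | 1215 |

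**Step 4. Where the 20 may come from.** 20/94 = 21.3%, so the addition resembles 20% of the required number. The shortcut 94 × (1 + d) gives 112.8 at 20%, 117.5 at 25% and 122.2 at 30%. Even that shortcut reaches no more than 114 only near the lower end of the range.

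**Step 5. Pooled over centres.** 114 × 3 = 342 per group. Remaining: 342 × 0.80 = 273.6 and 342 × 0.70 = 239.4 per group. Overall: 1026 × 0.80 = 820.8 and 1026 × 0.70 = 718.2.

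**Step 6. What the 94 itself stands for.** The formula is read here as n = Z²P(1 − P)/D², taking the division sign as lost in the text. P is 0.049; Z and D are not given. Assuming Z = 1.96, Z²P(1 − P) = 0.179. Then D = 0.05 gives 72, D = 0.04 gives 112, and 94 needs D of about 0.0436. The 94 therefore cannot be verified, and it concerns the precision of one prevalence estimate, not a comparison of groups.

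**Step 7. Scale, on assumptions the plan does not state.** For a two-sample t-test with two-sided 5% alpha and 80% power, the detectable difference per centre is 0.41 SD at 94 per group, 0.42 SD at 91 and 0.45 SD at 80. Pooled, it is 0.240 SD at 274 per group and 0.257 SD at 239.

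**The case against.** The arithmetic is hard to dispute, so the case on the other side is about scope and consequence. Most of it stands.

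- **The target is per centre.** The phrase about each recruiting centre is attached only to the final 342, and the article describes no analysis by centre. Pooled, 239 to 274 per group remain, far above 94. The per-centre reading is still the natural one, because 114 per group per centre is repeated in the Abstract and the objectives, but the point must be confined to it. A reader might multiply 94 by nine group-by-centre cells and hold the study to 846 overall. The article sets no such target.
- **No power is known to be lost.** A reader might infer that the group comparisons become underpowered. The 94 was not derived from any comparison, endpoint, standard deviation, alpha or power, so falling below it says nothing definite about power. On the assumptions in step 7 the change is modest.
- **The four-week visit.** It is tempting to say that the recovery comparison falls below its required number. The article warns that this visit may be missed, but it ties neither the 94 nor the 20–30% loss to that visit. It also leaves the handling of missing data to the statistical analysis plan, which is not at hand.
- **The number was also chosen to resemble EndoAfrica.** That may explain the 20. It does not make the 20 an adequate allowance for the rate that the sentence gives as its reason.

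What does not yield is the contradiction among the printed figures. The required number, the rate and the addition are all stated, and the addition is too small throughout the stated range.

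**Conclusion.** The stated allowance is wrong against the plan's own inputs. With 114 per group per centre, loss is covered up to 17.5%. At 20–30% loss, about 91 to 80 remain where 94 are called required, a gap of about 3 at the lower end of the range and 14 at the upper. The gap is trivial at 20% and material at 30%.

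This rests only on the printed 94, 20 and 20–30%, and on reading 94 as applying to each group at each centre. It does not show that the pooled study is too small or that any planned comparison loses a known amount of power. As an error in the central sample-size sentence, with a limited and unquantified effect on the analyses, it is minor to moderate.

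**What to change.** Keep 114 per group per centre and restate the sentence, for example:

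> 114 per group per centre allows for up to 17.5% loss; at 20–30% loss, 80–91 per group per centre (about 239–274 per group pooled, 718–821 overall) are expected to remain.

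This costs one sentence and a slightly less favourable stated figure, with no extra participants.

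If 94 retained per group per centre is to stand, correct the enrolment figure to 118 (20% loss) up to 135 (30% loss), and carry it through the per-centre and overall totals wherever they appear. That means 1062 to 1215 overall, or 36 to 189 more than 1026. It is the costlier route, since 'Possible limitations' already expects difficulty in recruiting ART-naïve participants.

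A detectable difference is optional. If one is quoted, such as 0.41 SD at 94 and 0.45 SD at 80 per group, label it as assuming a two-sample t-test, two-sided 5% alpha and 80% power, none of which the article states.

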## Discussion

The described project ENDOCOVID, an extension of the *EndoAfrica* study, will provide new data from the SSA context. No previous longitudinal studies in SSA have been carried out to comprehensively evaluate cardiovascular risk and vascular endothelial changes in COVID-19 patients with and without HIV/AIDS. The study will also provide more information related to the outcomes (severity of cases, ICU admissions, mortality rates) in persons with co-infections. The results will be innovative, as currently little is known about the effect of COVID-19 on PLHIV (+/−ART), especially in SSA. Repeated measurements over time will give us valuable knowledge about the progression or regression of markers of cardiovascular risk and disease in COVID-19 and HIV-infected persons. The information obtained from this project is important for developing guidelines and recommendations towards the management of cardiovascular health in patients with COVID-19 and HIV-infection for key stakeholders, including regional health care authorities. The findings of the ENDOCOVID project will furthermore contribute to the current global knowledge based on COVID-19 and HIV and its association with cardiovascular diseases.

The vascular and endothelial endpoints of the ENDOCOVID project will generate novel research data in the South African context and have big potential to improve the prediction of future cardiovascular events not only during COVID-19 but also for other diseases. While some studies have examined the reported association of endothelial dysfunction in COVID-19 patients, only very little information about SSA populations which are at the same time HIV-infected, is currently available. The use of three independent, non-invasive imaging techniques and the measurement of serum biomarkers related to endothelial health and coagulation improve the novelty of the project and also underline its strengths.

## Dissemination

Topics suggested for presentation or publication will be circulated to the principal investigators of the ENDOCOVID study. As part of community engagement, radio and television programmes as well as the social media (LinkedIn, ResearchGate) will be used. Results will be presented at the EACS: 18th European AIDS Conference (2021), IAS: 11th International AIDS Society Conference on HIV Science (2021), CROI: Conference on Retroviruses and Opportunistic Infections (CROI) (2021) and in journals such as AIDS, Clinical Microbiology and Infection, Lancet HIV. Output from this study will be communicated to the South Arican and Nigerian governments through Ministeries of Health.

### Possible limitations

Although the ENDOCOVID project will provide us a lot of new information, it is associated with several risks for which have been proposed impact alleviation strategies. These risks include:
All HIV-infected patients in South Africa must immediately begin with ART and it may limit our ability to recruit ART naïve participants. All of these untreated HIV-infected participants will serve as their own untreated controls during the cycle of our project, and we will be able to observe endothelial changes after initiation of ART.Lack of patients because of current lockdown and low prevalence of COVID-19 in SSA region. This may require that we have to expand our cohorts to more regions. That is why we have included two partners from SSA: South Africa and Nigeria. It has also been seen in most parts of the world that the period following the lockdown is accompanied by an increase in the number of COVID-19 related infections. So, between the two countries, we should have no problem in recruiting the requied number of participants to reach statistical significance for this study.The severity of the disease can limit our collection of samples and data about the patient, especially in those cases where the patients with COVID-19 are in the intensive care units and difficult to access for research purposes. However, we will work with clinicians to ensure that we can also evaluate the patients during acute care. Furthermore, patients at home and discharged from the hospital will also be recruited and their data collected. The complete data collection will be done by motivated healthcare partners of this project.It is possible that at the end of the project, we could be confronted with missing data. As missing data can limit the statistical comparisons across groups, we will reduce this via close collaborations with hospital personnel. In addition, we will take the required measures in the statistical analysis plan to deal with missing data.A possible limitation of this project is that it may not always be possible to collect post discharge data at 4 weeks. This may arise due to issues with patitence compliance and/or lockdowns. Every patient will be advised to report back 4 weeks post-discharge for a follow up assessment. Unpredictable and unplanned lock-downs, however, could make post-discharge data collection difficult.Another obvious limitation related to FMD and IMT measurements is the fact that these measurements are operator dependent and how inter-operator variability. It is also important that same vascular regions are measured in each participant at the 4–6 weeks’ follow-up visit. These risks will be reduced by limiting the number of operators in the research team, and training them intensively, and ensuring strict quality control steps by independent experts in this field.As the ART regimens differs across the recruitment sites, and different types of ART may have different effects, it could potentially influence the data that will be collected across the two SSA countries. When analyzing and interpreting the data from the different sites, details of the ART regimes will also be taken into account.

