**Fig. 1 Fig1:**
[figure not shown]
Project aims and objective established for the ENDOCOVID project. Shown are also the partner institutions and the impacts of the project

Three groups of participants will take part in this project:
PLHIV without ART but with COVID-19 (*n* = 114 in each recruiting center)PLHIV with ART and COVID-19 (*n* = 114 in each recruiting center)HIV-negative patients with COVID-19, sex−/age-matched (*n* = 114 in each recruiting center)

The following objectives will be investigated (Fig. 1):
Prevelance of PLHIV among those admitted for COVID-19 to clinics in South Africa and Nigeria.Assessment of the incidence of acute respiratory distress syndrome, admission to ICU, fatal course of disease (30-days mortality), and thromboembolic events in hospitalized patients included in the study.Evaluation of the influence of ART on severity of COVID-19 in PLHIV (with or without ART) as well as clinical presentation, changes of endothelial/vascular function and biomarkers.Evaluation of the effects of COVID-19 on endothelial/vascular function and thrombotic factors over infection and after recovery.Correlation of hospitalization and mortality of COVID-19 infected PLHIV (with or without ART) and HIV negatives with co-morbidity incidence;Assessment of the incidence of obesity and insulin resistance in the 3 groups.

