### Participant recruitment and study groups

#### Inclusion criteria

Participantsof the ENDOCOVID study population are patients with COVID-19, who at the same time are infected with HIV (with or without ART), or are HIV negative. Some may be admitted in the ICU. Participants will be recruited by qualified and trained researchers at hospitals based on pre-determined inclusion criteria. For inclusion into the study, participants must be positive for SARS-CoV-2 RNA and 18 years or older. Participants will be excluded from the study if they are less than 3 months post-partum and those with other co-infections than HIV such as tuberculosis (Fig. 2). Participants fulfilling the criteria will be invited into the study and asked to provide written informed consent.

Presence of SARS-CoV-2 RNA will be determined by real-time PCR. Subsequently, potential participants with unknown HIV status will be tested for HIV-infection via a rapid HIV test. A negative HIV test will be used to assign the participants to the HIV-negative group and a positive HIV test to the HIV-positive group, which is further split into two sub-groups according to the ART status of participants. Firstly, participants without ART as the “HIV-positive ART naïve” group. However, it has to be taken into consideration that, the majority of participants in this sub-group will start with ART, soon after recruitment. The third group are patients diagnosed as “HIV-positive on ART”. Therefore, we can evaluate cardiovascular risk and early endothelial changes in both the untreated and treated groups. SARS-CoV-2 RNA, CD4+ T-cell count, and HIV RNA viral load of the HIV-positive participants will be determined at admission (baseline), weekly, at discharge and, 4 weeks post-discharge (if possible) (Figs. 1 and 2). Participants are also required to refrain from smoking, drinking coffee or alcohol, or doing exercise for 4 h prior to the study. The menstrual phase of each female will be recorded.

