### Assessments: clinical and laboratory investigations

#### Health questionnaire, cardiovascular measurements, blood chemistry

General information will be obtained from a health questionnaire which include details about cardiovascular health including family and personal history of CVD, medication, smoking, and alcohol consumption (for detailed information, please find the full questionnaire in the supplementary material). Additionally, personal data about participants and their demographic characteristics based on the National Cholesterol Education Program Adult Treatment Panel III (NCEP ATP III) will be collected. Aspects related to the usage of medication, presence of co-infections and HIV disease characteristics (first diagnosis and duration of HIV infection, past and current regimens of ART treatment, viral load, nadir/current CD4+ T-cell count) will also be recorded [31]. Cardiovascular risk factors will be screened through analyses of (i) Lipid profile, (ii) glucose, (iii) glycated hemoglobin (HbA1c), (v) liver function enzymes, and (vi) high sensitivity hs-CRP, (vii) heart rate, (viii) blood pressure and (ix) body anthropometrics [32]. Together with evaluation of SARS-CoV-2 and HIV infection, these measurments in the participants will allow identification of common cardiovascular risk factors: smoking, alcohol consumption, overweight/obesity, hypertension, diabetes mellitus, dyslipidemia, renal impairment, inflammation, and liver disease.

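### Untreated PLHIV cannot act as their own controls for vascular change after ART start, because ART begins near admission and its effect is mixed with recovery from COVID-19

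*Protocol article*

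**What the plan says.** Inclusion criteria forms the groups at recruitment and takes "participants without ART as the “HIV-positive ART naïve” group". It then states that "the majority of participants in this sub-group will start with ART, soon after recruitment", and concludes shortly afterwards that "we can evaluate cardiovascular risk and early endothelial changes in both the untreated and treated groups".

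Possible limitations returns to the point as a recruitment risk: "All HIV-infected patients in South Africa must immediately begin with ART". The remedy offered is "All of these untreated HIV-infected participants will serve as their own untreated controls during the cycle of our project", followed by the statement that "we will be able to observe endothelial changes after initiation of ART".

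Study design sets the measurements at admission, weekly, at discharge and, if possible, 4 weeks after discharge. In Aim and objectives, the third objective is the influence of ART on severity, clinical presentation, endothelial/vascular change and biomarkers. The fourth is the effect of COVID-19 on endothelial/vascular function and thrombotic factors during infection and after recovery.

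Data collection, management and statistical analysis names inter-group comparisons, regression adjusted for confounders that include medication, and a repeated-measures model for change within individuals.

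**The concern.** A within-person control works only if nothing else that moves the outcome changes between the untreated and treated periods. Here something else does: the participant is recovering from COVID-19. The fourth objective uses the same window and overlapping outcomes to measure that recovery, so one change would be offered as evidence for two effects.

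A second consequence follows for the group comparison. By the article's own account most of the group without ART will be on ART soon after entry. At later visits, entry group no longer describes exposure well for vascular outcomes and biomarkers.

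At stake is the vascular and biomarker part of the third objective. Recovery could be credited to ART, or slow or incomplete recovery held against it. The Discussion expects the results to inform guidelines.

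**Working it through.** The plan gives no figure for this point, so there is none to reproduce. The argument rests on the timeline; the numbers below only illustrate it.

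**1. Timeline.** From Study design, Inclusion criteria and Possible limitations:

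| Time | COVID-19 | ART in the group without ART at entry |
|---|---|---|
| Admission | acute | not yet started |
| Weekly visits | acute to recovering | started in most, soon after recruitment |
| Discharge, 4 weeks after | recovering or recovered | started in most |

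The two columns change together.

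**2. Own-control estimate.** Let R be the vascular change due to COVID-19 recovery and A the change due to starting ART.

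- Before-after change = R + A
- Error as an estimate of A = (R + A) − A = R

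No value of R is given. More participants do not reduce this error.

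**3. Illustration with A = 0.** Assume a recovery shift r, in SDs of within-person change, and a two-sided 5% one-sample test (normal approximation):

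P(significant) = Φ(r√n − 1.96) + Φ(−r√n − 1.96)

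Take n = 94, the article's per-group number in one center before the dropout allowance, and n = 94 × 3 = 282, the same group over three centers.

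| Assumed r | n = 94 | n = 282 |
|---|---|---|
| 0.1 | 16% | 39% |
| 0.2 | 49% | 92% |
| 0.3 | 83% | >99% |
| 0.5 | >99% | >99% |

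For r = 0.2 and n = 94: 0.2 × √94 = 1.94, and Φ(1.94 − 1.96) is about 0.49. The article does not specify this test; it is the simplest form of an own-control analysis.

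**4. Between-group contrast after admission.** Let s be the share of the initially untreated group on ART at a visit, and f the fraction of the full ART effect that a starter shows by then. Apart from other confounding, the on-ART versus untreated contrast is A_full − f·s·A_full = (1 − f·s)·A_full.

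- At admission s = 0: no dilution.
- Later, a majority means s > 0.5. With f = 1, less than half of the effect remains.
- With f = 0 there is no dilution.

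Neither s nor f is given, so the direction (towards no difference) is clear if f > 0, but the amount is not.

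**5. Difference in change.** Set the starters' change against that of a concurrent group whose ART status is stable:

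(R_starters + A) − R_comparators = A + (R_starters − R_comparators)

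This equals A if recovery is similar in both groups. The smallest difference detectable with 80% power, in SDs of change, is (1.96 + 0.84) × √(2/n): 0.41 for 94 per group and 0.24 for 282 per group. The before-after test has 2.80/√n, that is 0.29 and 0.17. The loss is a factor of √2.

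**The case against.** The best defence is that the design already holds what is needed. The on-ART and HIV-negative groups follow the same schedule, a repeated-measures model is planned, medication is among the covariates, and nothing commits the analysis to a one-group before-after test. Time-varying ART terms and group-by-time contrasts are commonly left to an SAP, which is not shown. All this is fair: their absence is not the finding, and the error rates above are illustrative only. What remains is that the article names the participants' own untreated state as the control and presents it as the answer to a stated risk. A later SAP can replace that inference but cannot make it valid.

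Weekly visits could help separate ART start from time since admission if start dates varied widely. The text places most starts soon after recruitment, so little separation can be expected. Immediate start is stated only for South Africa. Patients at home or already discharged may also be recruited; their recovery component may be smaller, but it remains unknown.

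Several stronger readings are tempting, and the documents do not support them:

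- **Every ART comparison is mixed with recovery.** The admission comparison involves no within-person recovery, though it has confounding of its own. ART status at admission is a legitimate exposure for severity outcomes.
- **The own-control estimate would have the wrong sign.** That depends on values chosen for R and A. The article gives neither.
- **Starters will be analysed as untreated throughout.** No reclassification rule is given, but the article says that the early start has to be considered.
- **The ART start date is not collected.** The questionnaire is in supplementary material that is not reproduced.
- **People who stopped ART are counted as never treated.** This rests on loose use of two terms. The article records "past and current regimens of ART treatment" and does not say that such people will enter this group.

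**Conclusion.** The point holds for the own-control claim. Within person, ART start and COVID-19 recovery share one time axis, so the before-after vascular change cannot isolate the effect of starting ART. The bias equals the recovery component, of unknown size and direction. This rests on the stated timing of ART start and the measurement schedule, and on recovery moving the vascular outcomes, which the fourth objective sets out to measure.

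The later untreated versus treated contrast of vascular outcomes and biomarkers is also diluted, to the extent that newly started ART already acts on them.

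This should be fixed. It concerns the vascular and biomarker part of one of six objectives and can be cured in the analysis without changing any treatment or visit.

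**What to change.** - Withdraw the own-control claim under Possible limitations. Say instead that change after ART start includes recovery from COVID-19.
- Use the admission measurement, taken before ART start, for the with/without-ART contrast of vascular outcomes and biomarkers. Keep ART status at admission as the exposure for severity outcomes.
- For later visits, enter ART as a time-varying exposure by start date in the planned repeated-measures model. Confirm that the questionnaire captures the date, and add it if not.
- Estimate the ART-start effect as a difference in change against the concurrent on-ART and HIV-negative groups. State the assumption of similar COVID-19 recovery across groups, and show the result against each comparator separately, since disagreement would cast doubt on it.

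The cost is wording, possibly one date field, less precise ART-start estimates (about 0.41 rather than 0.29 SD detectable with 94 per group) and more modest claims about ART initiation.
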